## Abstract

**Background:**

Diarrhoea-associated mortality and morbidity are highest in infants and young children in low-income and middle-income countries (LMICs). Zinc supplementation during acute diarrhoea has been shown to reduce the duration of illness and the risk of persistent diarrhoea. However, vomiting with zinc supplementation is a common side effect that may interfere with compliance and programmatic scale-up, and may be related to the dose prescribed.

**Methods/design:**

The Zinc Therapeutic Dose Trial (ZTDT) is a two-centre (Tanzania and India), three-arm randomised, double-blind controlled non-inferiority trial. Children 6–59 months of age with acute diarrhoea are eligible to participate. Enrolled children (1500 per arm; 4500 total) will be randomly allocated to receive 5, 10 or 20 mg of zinc sulfate daily for 14 days and will be followed up for 60 days after enrolment. All children will receive WHO/Unicef Integrated Management of Childhood Illness standard of care (oral or intravenous rehydration and zinc as indicated and feeding advice). The primary efficacy outcomes of the trial are the percentage of subjects with diarrhoea duration >5 days, the mean total number of loose or watery stools after enrolment and the proportion of children vomiting within 30 min of zinc administration.

**Discussion:**

The ZTDT trial will determine the optimal dose of therapeutic zinc supplements for treatment of acute diarrhoea in children aged 6–59 months in two LMICs. The results of the trial are likely to be generalisable to childhood acute diarrhoea in similar resource-limited settings and may influence global policy about zinc supplementation dosage during acute diarrhoea.

**Trial registration number:**

NCT03078842.

**Trial status:**

Enrolment began in January 2017 and follow-up is estimated to be completed by April 2019. As of 1 February 2019, 742 children are still contributing data to the ZTDT study.

What is already known on this topic?Therapeutic zinc supplementation has been recommended by WHO/Unicef for standard diarrhoea case management since 2004.Research evidence had shown zinc reduced the duration and severity of the acute diarrhoea, and lowered the risk of persistent diarrhoea.However, many trials noted that current dosage (20 mg/day for children aged >6 months) is associated with vomiting and possibly poor compliance.

What this study hopes to add?This study evaluates whether lower doses of zinc (10 mg/5 mg) are non-inferior to the standard dose in efficacy but superior for vomiting.If vomiting is less frequent and efficacy is maintained with low-dose zinc, caregiver acceptability may improve, leading to greater utilisation and better health outcomes.

## Background

Zinc is a vital micronutrient essential for protein synthesis, cell growth and differentiation, immune function, and intestinal transport of water and electrolytes.^1^ Zinc is also important for normal growth and development of children both with and without diarrhoea.^2^ Zinc deficiency is associated with an increased risk of gastrointestinal infections, altered structure and function of the gastrointestinal tract and impaired immune function.^3–5^ Dietary deficiency of zinc is especially common in low-income countries because of a low dietary intake of zinc-rich foods (including foods of animal origin) or low bioavailability due to the presence of phytates often found in cereal-based diets.^1^

The benefits of zinc supplementation in the management of diarrhoea have been observed in several studies. Patel *et al*
6 noted in a systematic review and meta-analysis an approximate 20% reduction in the mean duration of acute diarrhoea with zinc supplementation. Lazzerini and Wanzira,^7^ summarising data from 2581 children from 9 trials, noted that children older than 6 months receiving zinc supplements had a shorter diarrhoea duration by about half a day (mean difference −11.46 hours, 95% CI −19.72 to −3.19). A reduction in diarrhoea that continues up to day 7 (risk ratio 0.73, 95% CI 0.61 and 0.88) was also noted in this study. Moreover, the study indicated that zinc supplements in children with persistent diarrhoea (defined as diarrhoea for >14 days) also may shorten average diarrhoea duration by 16 hours (mean difference −15.84 hours, 95% CI −25.43 to −6.24). As a result of these and other trials, since 2005 WHO/Unicef have recommended routine zinc supplementation (10 mg daily for infants below 6 months of age; 20 mg daily for children older than 6 months) for 10–14 days.^8^

These doses, however, were not chosen after dose-ranging studies, and substantially exceed the recommended dietary allowances (RDA) for zinc in infancy and early childhood (2–5 mg/day).^9^ High doses of zinc can cause epigastric pain and lethargy, and its metallic taste can also induce vomiting. Vomiting with zinc supplements is a common side effect noted in many published trials. A meta-analysis by Lukacik *et al*
3summarised the findings for acute and persistent diarrhoea from a total of 22 zinc intervention trials, using a range of zinc dosing (5–45 mg/day). In 11 acute diarrhoea trials (n=4438), the proportion of participants who vomited after the initial dose was significantly higher with zinc use than with placebo (12.7% vs 7.6%; relative risk [RR]: 1.55; 95% CI: 1.30 to 1.84; p≤0.001). According to the review by Lazzerini and Wanzira,^7^ the risk of vomiting increased with zinc supplementation in both children older than age 6 months (risk ratio 1.57, 95% CI 1.32 to 1.86; 2605 children, 6 trials) as well as children younger than 6 months of age (risk ratio 1.54, 95% CI 1.05 to 2.24; 1334 children, 2 trials). Other studies have also reported that therapeutic zinc supplementation during diarrhoea causes higher rates of vomiting.^10–12^

Thus, although substantial evidence supports the efficacy of zinc supplementation during episodes of diarrhoea, vomiting is significantly more common among supplemented children. Lower doses of zinc, provided they are equally effective, might have the advantage of reducing side effects, increasing compliance and programmatic roll-out. If the zinc dose for diarrhoea treatment and zinc deficiency can be uniform, then the national essential drug lists can be simplified. Therefore, there exists an important rationale to identify the dose of zinc supplementation associated with both efficacy and an improved safety profile. We present the protocol for a two-centre, randomised, double-blind controlled trial of three doses of zinc conducted in Tanzania and India. The overall goals of the study are to evaluate the non-inferiority, safety and acceptability of the two lower zinc doses (5 and 10 mg/day) versus standard zinc dose (20 mg/day).

## Methods

### Study design

The Zinc Therapeutic Dose Trial (ZTDT) is an individually randomised, parallel-group, double-blind, controlled trial of three doses of supplemental zinc conducted among 4500 children aged 6–59 months in India and Tanzania (ClinicalTrials.gov identifier NCT03078842).

The trial protocol was developed by collaborators at WHO, Department of Maternal Newborn, Child and Adolescent Health (Geneva, Switzerland) together with teams in New Delhi, India (Centre for Public Health Kinetics), Dar es Salaam, Tanzania (Muhimbili University of Health and Allied Sciences) and Boston, USA (Boston Children’s Hospital and Harvard TH Chan School of Public Health). The ZTDT protocol diagram is presented in online supplementary additional file 1. The schedule of trial enrolment, interventions and assessments is presented in online supplementary additional file 2. The first participant was enrolled in the trial in January 2017 in India and March 2017 in Tanzania and follow-up data collection will continue through approximately April 2019. This paper follows the Standard Protocol Items: Recommendations for Interventional trials (SPIRIT) checklist (see online supplementary additonal file 3).

10.1136/bmjpo-2019-000460.supp1Supplementary file 1

10.1136/bmjpo-2019-000460.supp2Supplementary file 2

10.1136/bmjpo-2019-000460.supp3Supplementary file 3

The study population will include 4500 children aged 6–59 months with diarrhoea of <72 hours duration. Enrolled children will be followed up for 60 days after randomisation. The participant will be followed up closely for the first 15 days to record postintervention morbidity outcomes and to ensure compliance with study regimen. Study participants will be assessed again at 30, 45 and 60 days postenrolment to estimate impact on long-term morbidity outcomes.

### Patient and public involvement

This research was done without patient involvement. Patients were not invited to comment on the study design and were not consulted to develop patient relevant outcomes or interpret the results. Patients were not invited to contribute to the writing or editing of this document for readability or accuracy.

### Primary and secondary objectives

The overall aim of ZTDT is to identify the optimal dose of zinc in children under 5 years with acute diarrhoea.

The primary aims of the study are: (1) to assess whether lower doses of zinc (5 or 10 mg/day) are at least as effective as the standard dose of zinc (20 mg/day) in children aged 6–59 months, in terms of burden of illness (percentage of subjects with diarrhoea lasting >5 days; mean number of loose or watery stools during follow-up) and (2) to evaluate the improved effectiveness by reduction in the risk of vomiting in 30 min after receipt of the supplement in low-dose supplemental zinc (5 or 10 mg/day) in comparison to standard dose of zinc (20 mg/day).

Secondary aims of the study are: (1) to explore whether lower doses of zinc have any impact on postacute illness morbidity outcomes assessed at 30, 45 and 60 days, (2) to explore whether duration of treatment, estimated by mother’s reports and collection of used zinc blister packs, has any impact on the primary outcomes, (3) to determine the acceptability of low-dose supplemental zinc compared with standard zinc dose based on an acceptability scale and (4) to determine whether the different doses of zinc are associated with differential plasma zinc levels at days 3, 7, 15, 21 and 30 after randomisation.

## Participants/interventions and outcomes

### Study setting

The study recruitment sites are in South East Asia (SEA) and sub-Saharan Africa (SSA). In SEA, the study recruitment sites are located in Sangam Vihar, a resettlement colony on outskirts of South Delhi and Harsh Vihar, a semi-urban locality in North East District, Delhi, India. In SSA, recruitment sites are at health centres in Temeke District Hospital, Mbagala Round Table and Mbagala Rangi Tatu, Dar es Salaam, Tanzania. Both the sites will be recruiting from outpatient health facilities.

### Eligibility

Study participants will be eligible for enrolment in the study if they meet the following inclusion criteria: 1) male and female children between 6 and 59 completed months of age, 2) acute diarrhoea duration of <72 hours at the time of screening (defined as three or more loose or watery stools) or dysentery (defined as visible blood in the stool), 3) likely to stay within the study area for the next 2 months and 4) written informed consent is obtained from caretaker.

Children will be excluded if they: (1) have severe acute malnutrition (weight for length/height z-score of <−3 or oedema), (2) have severe dehydration that cannot be corrected within 4–6 hours, (3) have signs of severe pneumonia (characterised by presence of either chest in-drawing and either of the following: convulsions or unconscious or vomiting everything,^13^ sepsis, rapid diagnostic test (RDT)-confirmed malaria or other severe illness, (4) have previously or currently been enrolled in the study, (5) are currently enrolled in another trial, (6) are not intending to remain in study area for the duration of the study, (7) have a caregiver who declines participation in the study, (8) have other child currently enrolled in the study in the same household and (9) have used zinc supplements during the 3 days preceding study enrolment.

### Sample size

We will enrol 4500 children (1500 per study arm) in the trial. Table 1 presents sample size assumptions and calculations for each of the three primary outcomes. The total sample size for the trial was selected to have at least 90% power for each of the primary outcomes. The primary outcomes (mean number of loose or watery stools postrandomisation and percentage of children with diarrhoea for >5 days) are both based on the non-inferiority hypotheses, while the primary outcome of vomiting postdose assumes a superiority hypothesis. We assumed 1:1:1 randomisation between the three treatment arms, a nominal type I error rate (α) of 0.05% and 5% loss to follow-up rate.

**Table 1 T1:** Sample size calculations for the primary trial outcomes

Outcome	Value in standard dose (20 mg/day) group	Expected value in low-dose groups	Non-inferiority margin	Power, significance level	Sample size per arm (with ~5% attrition)
Duration of diarrhoea, mean (SD)	3.0 (2.7) days	3.0 (2.7) days Lower dose equally effective	0.3 days	90%, 5%	1460
Percentage of children with diarrhoea >5 days	16%	16% Lower dose equally effective	+4%	90%, 5%	1500
Total number of loose or watery stools during follow-up, mean (SD)	10 (9) stools	10 (9) stools Lower dose equally effective	+2 stools	90%, 5%	1460
Percentage of children with vomiting during follow-up	20%	15% Lower dose safer	Not applicable because of superiority hypothesis for this outcome	90%, 5%	1340

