### Analysis of primary outcomes

#### Primary outcome 1

Number (%) of subjects with diarrhoea episodes >5 days. The last day of diarrhoea will be defined as the day in which there is passage of the last liquid or semi-liquid stool prior to two diarrhoea-free days (days when less than three loose stools/day). The duration of diarrhoea will be defined as the number of days between randomisation (not the reported day of onset of diarrhoea symptoms before randomisation) and the last day with diarrhoea. Children who are lost to follow-up, die or withdraw before 5 days will be excluded from this analysis. For the primary analysis, we have set the threshold for non-inferiority of lower doses of zinc (10 or 5 mg/day) as compared with the standard 20 mg/day at <4% in absolute risk (risk difference) compared with the standard dose in the proportion of subjects with prolonged diarrhoea. The proportions of participants with a prolonged diarrhoea episode (defined as >5 days) will be calculated in all treatment arms, and the risk differences (and their 95% CIs) between the lower doses (5 and 10 mg/day) and the standard dose (20 mg) will be estimated. A Cochran-Mantel-Haenszel approach will be used to take stratifying randomisation factors, for example, country and age groups, into account. If the upper limit of the 95% CI for the risk difference is <4%, we will conclude non-inferiority for one or both lower dose arms. We will also examine the RR of prolonged diarrhoea episodes in both lower dose arms compared with the standard dose arm using RR regression which accounts for factors included in the stratified randomisation. In secondary analyses, Cox proportional hazard models will be used to estimate HRs and their 95% CIs for recovery from diarrhoea in each of the lower dose arms compared with the standard dose arm. The time to recovery is defined as the duration of diarrhoea as noted above.

#### Primary outcome 2

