Total number of loose or watery stools after enrolment. An analysis of covariance (ANCOVA) approach will be used to estimate the mean differences and their 95% CI in the total number of loose or watery stools after enrolment for each lower dose arm compared with the standard dose arm, while accounting for the stratified randomisation design. The non-inferiority margin was set at two stools, therefore if the upper limit of the 95% CI is less than two stools, we will reject the null hypothesis that the lower dose zinc is inferior to the standard dose in terms of reducing the total number of loose or watery stools.

#### Primary outcome 3

Vomiting within 30 min after administration of the trial regimen. We hypothesise that the lower dose of zinc will be associated with a reduced risk of vomiting and therefore a superiority test will be used. Vomiting within 30 min of each daily zinc dose is repeatedly measured during the 14-day administration period. Generalised estimating equations (GEE) with the log link, binomial variance and exchangeable correlation matrix will be used to assess the RR of vomiting among the three treatment arms. The exchangeable working covariance matrix and robust estimators of the variances will be used to construct CIs. The robust estimators are consistent estimators of the variances even if the working correlation matrix is misspecified. Stratified randomisation factors will be considered in the model. A secondary analysis concerning severe vomiting (defined as vomiting requiring hospitalisation or vomiting requiring intravenous fluids) will also be performed in similar fashions. We will also examine the proportion of children ever vomiting between the treatment arms and examine whether the RR of vomiting differs by follow-up day.

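### Primary outcome 1 has about 83–85% power under the protocol's 95% CI rule, not the stated 90%: the 1500 per arm matches a one-sided 5% test, while the rule is one-sided 2.5%

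*Protocol article*

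**What the plan says.** **Power claim.** The Sample size section of the protocol article states: "The total sample size for the trial was selected to have at least 90% power for each of the primary outcomes". The same paragraph gives "a nominal type I error rate (α) of 0.05% and 5% loss to follow-up rate".

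**Design inputs for primary outcome 1.** In Table 1, the row for diarrhoea beyond 5 days has 16% under the standard dose and "16% Lower dose equally effective" under the lower doses. The margin is +4%, the power and level entry is 90% and 5% with no sidedness, and the result is 1500 per arm including about 5% attrition.

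**Decision rule.** Analysis of primary outcomes, Primary outcome 1, sets the margin "at <4% in absolute risk (risk difference) compared with the standard dose". It plans risk differences with their 95% CIs and then uses the same interval to decide: "If the upper limit of the 95% CI for the risk difference is <4%, we will conclude non-inferiority". Primary outcome 2 uses the same form of rule: non-inferiority "if the upper limit of the 95% CI is less than two stools".

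**The concern.** A two-sided 95% CI leaves 2.5% in its upper tail, so comparing its upper limit with the margin is a one-sided test at 2.5%. If the sample size was worked out at one-sided 5%, the design and the decision rule use different error rates. The trial then has less power than it claims.

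The row affected is the one that gives the largest number in Table 1 and so fixes the trial at 1500 per arm. At stake is the chance that a lower dose that is truly equivalent fails to be shown non-inferior on diarrhoea beyond 5 days. Readers are told that this chance is at most 10% per comparison.

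**Working it through.** **Inputs**, all from the protocol article:
- Risk p = 0.16 in both groups, true difference 0 (Table 1).
- Margin d = 0.04 (Table 1; Primary outcome 1).
- Each lower dose compared with 20 mg at equal size: "We assumed 1:1:1 randomisation between the three treatment arms".
- "5% loss to follow-up rate", so 1500 × 0.95 = 1425 evaluable per arm.
- z for 90% power = 1.2816; z for one-sided 5% = 1.645; z for one-sided 2.5% = 1.960.

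**Step 1. Reproduce the 1500.**

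n per arm = 2p(1−p)(z_alpha + z_power)² / d², where 2 × 0.16 × 0.84 / 0.04² = 168.

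- One-sided 5%: 168 × (1.645 + 1.2816)² = 1438.7 evaluable; /0.95 = 1514 enrolled. This is within 1% of 1500.
- One-sided 2.5%: 168 × (1.960 + 1.2816)² = 1765.2 evaluable; /0.95 = 1858 enrolled. This misses by about 358 per arm.
- Treating the row as a superiority comparison of 16% with 20% gives 1663 to 2092 enrolled, depending on sidedness and continuity correction. None of these matches.

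**Step 2. Check the inferred level on another row.** Duration of diarrhoea (SD 2.7, margin 0.3, difference 0): n = 2 × 2.7² × (z_alpha + z_power)² / 0.3², where 2 × 2.7² / 0.3² = 162.

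- One-sided 5%: 1387.3; /0.95 = 1460. The table prints 1460.
- One-sided 2.5%: 1702.2; /0.95 = 1792.

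Both rows point to one-sided 5%.

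**Step 3. Power of primary outcome 1.** Power = Φ(d/SE − z_alpha), with SE = √(2 × 0.16 × 0.84 / n).

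| Evaluable per arm | SE | d/SE | One-sided 5% | One-sided 2.5% (95% CI rule) |
|---|---|---|---|---|
| 1425 | 0.01373 | 2.912 | 89.8% | 83.0% |
| 1500 | 0.01339 | 2.988 | 91.0% | 84.8% |

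**Step 4. The other two primary outcomes, as stated.**
- Stool count, SD 9, margin 2, n = 1425, one-sided 2.5%: d/SE = 2 / (9 × √(2/1425)) = 5.93, and power = Φ(5.93 − 1.96), above 99.9%.
- Vomiting, 20% against 15%, n = 1425, two-sided 5%: power about 94%. The row's 1340 is close to the two-sided 5% figure with continuity correction (1252 evaluable, 1318 enrolled). It is far from the one-sided figures (1040 to 1082 enrolled).

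**The case against.** **The one-sided 5% level is not stated.** Table 1 gives no sidedness, and the full protocol is not shown. This stands as a caveat on how the 1500 arose. The power figure does not depend on it: 83–85% follows from the printed inputs and the printed decision rule alone.

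**The interval might have been meant as a one-sided 95% bound.** Power would then be about 90%. But the text introduces the intervals as ordinary 95% CIs around the risk differences and uses them unchanged for the decision. It mentions neither a one-sided bound nor a 90% interval.

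**The loss may be smaller at day 5.** Only children lost before 5 days are excluded from this analysis, while follow-up runs to day 60. If the 5% covers the whole period, the evaluable number lies between 1425 and 1500. This stands, and is why the result is a range. Stratified analysis might add a little, but the article gives no figures for it.

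**The rule itself is sound.** This also stands. The 95% CI rule is the stricter of the two, so no positive finding is weakened.

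A reader might go further in three ways that the document does not support:
- *That every non-inferiority outcome is short of power.* Stool count is not, with its stated 2-stool margin. That row's 1460 does not match its margin (one-sided 5% gives 346.8/0.95 = 365 per arm), but this is a separate slip. It is no evidence about the error rate.
- *That the duration row shows a second underpowered primary outcome.* Duration as a mean is not among the three primary outcomes. It serves here only to identify the level used.
- *That the trial was planned at an alpha of 0.05%.* Every row of Table 1 says 5%, and a literal 0.05% would need roughly 3700 to 4000 enrolled per arm. It is a misprint.

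**Conclusion.** The point holds for primary outcome 1 only. The claim of at least 90% power for each primary outcome is not met under the protocol's own decision rule. Power for diarrhoea beyond 5 days is about 83% per dose comparison with 1425 evaluable per arm and about 85% with 1500. The chance of failing to confirm a truly equivalent dose is therefore 15–17%, not 10%.

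This assumes a 16% risk in both groups, a 4-point margin, the normal approximation, and no gain from stratification. Type I error is not affected. The error lies in the stated power, not in the validity of the test.

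**What to change.** In the Sample size section and Table 1:

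- Keep the 95% CI decision rule. Moving to a 90% interval would recover the printed power only by doubling the one-sided error from 2.5% to 5%.
- Restate power for primary outcome 1 as about 83–85% per dose comparison, with the evaluable numbers behind it, and drop the statement that each primary outcome has at least 90%.
- Label the level as one-sided 2.5% for the non-inferiority outcomes and two-sided 5% for vomiting. Change the power entry for primary outcome 1 at the same time, since relabelling alone would leave that row wrong.
- Correct the alpha of 0.05% to match.
- Do not introduce a 1-stool margin to explain the stool row. Deal with the mismatch between its 1460 and its +2 margin separately.

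This is wording only and needs no extra children. The price is a less favourable stated power for the outcome that set the sample size.

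### The sample size text gives the type I error rate as 0.05%, against 5% in every row of Table 1: apparently a misprint, and the correction must also state sidedness

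*Protocol article*

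**What the plan says.** All references are to the protocol article.

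- **Sample size, text.** The assumptions include "a nominal type I error rate (α) of 0.05% and 5% loss to follow-up rate". The section also states: "The total sample size for the trial was selected to have at least 90% power for each of the primary outcomes". Enrolment is fixed by "We will enrol 4500 children (1500 per study arm) in the trial".
- **Sample size, Table 1.** All four rows give 90% power and a 5% level. The row "Percentage of children with diarrhoea >5 days" has 16% in the standard arm, "16% Lower dose equally effective" in the low-dose arms, a margin of 4 points and 1500 per arm. The mean duration row has SD 2.7 days, a margin of 0.3 days and 1460 per arm. The vomiting row has 20% against 15% and 1340 per arm. No row says whether the 5% is one-sided or two-sided.
- **Analysis of primary outcomes.** For outcome 1 the margin is set "at <4% in absolute risk (risk difference) compared with the standard dose in the proportion of subjects with prolonged diarrhoea", and the rule is "If the upper limit of the 95% CI for the risk difference is <4%, we will conclude non-inferiority for one or both lower dose arms". For outcome 2: "The non-inferiority margin was set at two stools, therefore if the upper limit of the 95% CI is less than two stools".

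**The concern.** The text and the table beside it give error rates that differ by a factor of 100. The same sentence writes the attrition rate correctly as a percentage, so nothing tells the reader to take 0.05% as the proportion 0.05.

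The type I error rate is one of the figures on which the sample size and the power claim rest, and this is the only place where the prose names it. Taken literally, it promises far stricter control of false non-inferiority claims than the written rule delivers: an upper 95% limit is a one-sided 2.5% test, which is 50 times 0.05%. It also makes the 90% power statement impossible for outcome 1. A reader trying to reproduce the sample size from the text would fail.

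**Working it through.** **Inputs.** From Sample size and Table 1: 16% in both arms, margin 0.04, 90% power, 1500 per arm, 5% loss, so 1500 × 0.95 = 1425 analysed. For duration: SD 2.7, margin 0.3. For vomiting: 20% against 15%. All calculations use the normal approximation.

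**Formulas.**
- Two proportions, non-inferiority: n = (z_α + z_β)² × 2p(1 − p)/margin²
- Two means, non-inferiority: n = (z_α + z_β)² × 2 SD²/margin²
- Enrolled = n/0.95
- Power = Φ(margin/SE − z_α)
- z_β = 1.282. z_α = 1.645 (one-sided 5%), 1.960 (one-sided 2.5%), 3.291 (one-sided 0.05%), 3.481 (two-sided 0.05%).

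**Step 1: reproduce the printed sizes.** For outcome 1, 2 × 0.16 × 0.84/0.04² = 168. For duration, 2 × 2.7²/0.3² = 162.

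| Level | (z_α + z_β)² | Outcome 1: n, enrolled per arm | Duration: n, enrolled per arm |
|---|---|---|---|
| One-sided 5% | 8.564 | 1439, about 1514 | 1387, about 1460 |
| One-sided 2.5% | 10.507 | 1766, about 1859 | 1703, about 1793 |
| One-sided 0.05% | 20.90 | 3512, about 3697 | 3387, about 3565 |
| Two-sided 0.05% | 22.68 | 3811, about 4011 | 3675, about 3868 |
| **Printed** | | **1500** | **1460** |

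One-sided 5% gives 1460 for duration (1462 if n is rounded up before the attrition step) and comes within 1% of 1500 for outcome 1. At 0.05% both rows need more than twice the printed size.

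The vomiting row (printed 1340) comes closest at two-sided 5% with continuity correction: 1252 analysed, 1318 enrolled. At 0.05% it would need between 2539 and 2797 enrolled, depending on sidedness and continuity correction.

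The stool-count row does not help to identify the level. With its printed margin of 2 stools and SD 9, one-sided 5% gives 366 per arm and 0.05% gives 892 (one-sided) or 968 (two-sided). None of these is near the printed 1460.

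**Step 2: power for outcome 1 with 1425 analysed.** SE = √(2 × 0.16 × 0.84/1425) = 0.01373, and 0.04/0.01373 = 2.912.

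- One-sided 5%: Φ(2.912 − 1.645) = 89.8%
- One-sided 2.5% (the upper 95% limit): Φ(2.912 − 1.960) = 83.0%
- One-sided 0.05%: Φ(2.912 − 3.291) = 35.3%
- Two-sided 0.05%: Φ(2.912 − 3.481) = 28.5%

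With all 1500 analysed, the four figures are 91.0%, 84.8%, 38.1% and 31.1%.

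**Step 3: what replacing 0.05% by 5% settles.** It makes the text agree with Table 1. It does not make the text agree with the interval rule for non-inferiority. The non-inferiority sizes rest on one-sided 5%, the vomiting row fits two-sided 5%, and the upper limit of a 95% interval is one-sided 2.5%. A bare 5% therefore means different things in different rows.

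**The case against.** The strongest reply is that this is a stray percent sign. The right level stands in all four rows of the adjacent table, no sample size or decision rule depends on 0.05%, and the correction changes neither enrolment nor analysis. All of that stands, and it limits the weight of the point. It does not remove it, because a core design figure is wrong as printed and is contradicted in its own section.

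Two stronger readings are tempting, and the article supports neither.

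- **That the trial has about 35% power for outcome 1.** A reader might infer this from the text alone. The printed sizes were evidently built at 5%, so the 28% to 35% range serves only to show that 0.05% was not the level used.
- **That the interim stopping boundaries were set at the wrong level.** The Monitoring section names O'Brien-Fleming boundaries but does not link them to the figure in Sample size. It refers to a statistical analysis plan that is not at hand. Harm by this route is speculative.

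It could also be said that sidedness is a separate matter from the misprint. It is, but the correction cannot be written properly without it. Otherwise the corrected sentence would appear to support a 90% claim that the interval rule does not meet for outcome 1.

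**Conclusion.** The point holds as an internal contradiction, apparently a misprint for 5% (0.05). The stated 0.05% matches neither the level in Table 1, nor the printed sample sizes for outcome 1, duration and vomiting, nor the 95% interval rules. For outcome 1 it would imply about 28% to 35% power with 1425 analysed, or about 3700 to 4010 enrolled per arm for 90%.

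Once the level is corrected, a gap remains. The non-inferiority sizes reproduce at one-sided 5%, while the written rule is one-sided 2.5%. Under that rule, power for outcome 1 is about 83% (1425 analysed) to 85% (1500), and 90% would need about 1859 enrolled per arm.

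These figures assume the Table 1 inputs, no true difference between doses, an unstratified comparison and the normal approximation. The conclusion that 0.05% was not used is insensitive to sidedness and attrition, since power at that level stays between 28% and 38% across all the cases tried.

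**What to change.** In the Sample size text, replace 0.05% with 5% (0.05), and state for each primary outcome whether the level is one-sided or two-sided.

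Do not present this edit as agreement with the 95% interval rule. Reconcile the power statement with the rule actually used: either report about 83% to 85% for outcome 1 under the upper 95% limit, or explain that the sizing used one-sided 5% while the analysis applies a stricter criterion. If the overall level for the O'Brien-Fleming boundaries is mentioned alongside, give its sidedness so that it is consistent with the interval rule; otherwise leave it out of this correction.

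The cost is one corrected figure and a sentence or two of text. Enrolment and the planned analyses do not change.
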